#### Power analysis

The probability to find a significant effect with 50 included participants per group, a dropout rate of 15%, a small true effect size of *f* = 0.1, pretest-posttest correlation of *r* = .85, and an α-error of 0.05 is 90%. We used G*Power 3.1.6. for power analysis [55].

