## Methods

The Jigsaw *P*uzzles *A*s *C*ognitive *E*nrichment (PACE) study will take place at Ulm University, Germany, as a randomized, active-controlled, assessor-blinded superiority trial with two parallel groups. Between March and approximately October 2016, we will include and randomly assign 100 cognitively healthy, middle-aged and older adults (age 50 years and above) to a jigsaw puzzle group or a cognitive health counseling group with a 1:1 allocation ratio in blocks of four, stratified by cognitive status and age. Participants in the jigsaw puzzle group will engage in 30 days of solving jigsaw puzzles (6 days/week over a period of 5 weeks for at least 1 h/day) and receive cognitive health counseling (15-minutes face-to-face counseling plus three telephone calls). The cognitive health counseling group will receive the same counseling intervention but will not solve any jigsaw puzzles during the intervention period. The SPIRIT 2013 Checklist provides an overview about the contents of this study protocol (see Additional file 1).

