### Statistical analysis

The primary efficacy analysis will be based on mixed-effects models' group × time interaction [53] in an intention-to-treat approach [54] that includes all randomly assigned participants with follow-up observations. Effect sizes will include standardized differences in the pretest-posttest change scores between both groups. Standardization will be based on (1) baseline scores and (2) pretest-posttest change scores. In additional analyses, we will account for potential confounding variables such as baseline performance, the number of challenging social, physical, and cognitive activities performed in the past 4 weeks, the pretest-posttest change in these activities, Mediterranean diet in the past 4 weeks, and pre-posttest change in diet, age, education, participants’ test motivation at the posttest assessment, and their expectations of cognitive benefits.

As the primary intention-to-treat analysis is a conservative method, which may underestimate the true effect size of solving jigsaw puzzles for individuals who follow the protocol, we will use a supportive per-protocol analysis, which includes only participants who completed at least 80% of the jigsaw puzzle protocol (≥24 jigsaw puzzle days with a minimum of 45 min). With this supportive analysis, we do not only assess the robustness of effects, but may also receive a more accurate estimate of the true effect size given optimal conditions.

For subgroup and moderator analyses, pre-specified variables comprise baseline global visuospatial cognition, amount of lifetime puzzle experience, number of challenging social, physical, and cognitive activities within the intervention period, age, MMSE, and experienced pleasure in solving jigsaw puzzles.

Finally, we will assess cognitive demands of solving jigsaw puzzles and the transfer potential of gains in jigsaw puzzle skill on gains in the study outcomes by calculating the correlation between jigsaw puzzle skill in the 40-piece puzzle and the study outcomes at baseline.

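### The 90% power is described as power for a small effect, but in the calculation that yields it f = 0.1 is a between-group difference in change of 0.40 baseline SD (0.73 change-score SD)

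*Protocol article*

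**What the plan says.** The section *Power analysis* of the protocol article begins "The probability to find a significant effect with 50 included participants per group, a dropout rate of 15" per cent. It then assumes "a small true effect size of *f* = 0.1, pretest-posttest correlation of *r* = .85" and an alpha of 0.05, arrives at 90%, and names G*Power 3.1.6 as the software.

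The section *Statistical analysis* makes the group × time interaction the primary test. On reporting it says: "Effect sizes will include standardized differences in the pretest-posttest change scores between both groups". It names two standardizers, the baseline scores and the pretest-posttest change scores. The article does not convert f = 0.1 to either scale.

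**The concern.** The size of effect that an f of 0.1 stands for depends on the design. When two groups are compared at one time point, f is half the standardized difference, so f = 0.1 is a difference of 0.20 SD, which is conventionally called small. In a 2 × 2 group × time interaction, f is a quarter of the difference in change, so the same f is twice that difference. If the 90% comes from the interaction calculation, the label fits a different comparison from the one that was powered.

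What is at stake is the design property the article advertises. A reader who takes 90% power for a small effect at face value will think the trial much more sensitive than it is on the scales it will report.

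**Working it through.** **Inputs.** From *Power analysis*: 50 per group, 15% dropout, f = 0.1, r = .85, alpha 0.05. From *Methods*: 1:1 allocation. From *Statistical analysis*: a group × time interaction, here with k = 2 groups and m = 2 time points. Completers: 100 × 0.85 = 85 (84 if rounded to 42 per group).

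**Step 1: reproduce the 90%.** For the repeated-measures within-between interaction, lambda = f² × N × m / (1 − r), tested on F(1, N − 2).

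- N = 85: lambda = 0.01 × 85 × 2 / 0.15 = 11.33, power 91.4%.
- N = 84: lambda = 0.01 × 84 × 2 / 0.15 = 11.20, power 91.1%.

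Other ways of using the same inputs at N = 85 do not come near 90%:

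- f² × N = 0.85 gives 15%.
- f² × N × m = 1.70, ignoring r, gives 25%.
- f² × N / (1 − r) = 5.67, without m, gives 65%.

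The stated figure therefore identifies the calculation, and the calculation fixes what f means.

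**Step 2: convert f to a difference in change.** Let D be the between-group difference in mean change and σ the baseline SD, taken as equal at both time points. The variance of change is 2σ²(1 − r). A two-sample t test on change scores with N/2 per group has squared noncentrality D² × N / (8σ²(1 − r)). Setting this equal to f² × N × 2 / (1 − r) gives D² = 16f²σ², so D = 4fσ.

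- On the baseline scale: D = 4 × 0.1 = 0.40 SD. As a check, cell means of 0 and 0.40 in one group and 0 and 0 in the other give interaction effects of ±0.10, hence f = 0.10.
- On the change scale: SD of change = √(2 × 0.15) = 0.548, and 0.40 / 0.548 = 0.73 SD.

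**Step 3: power at smaller differences.** With N = 85, r = .85 and two-sided alpha 0.05, lambda = D² × 85 / (8 × 0.15) = D² × 85 / 1.2.

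| D, baseline SD | D, change SD | lambda | Power |
|---|---|---|---|
| 0.40 | 0.73 | 11.33 | 91% |
| 0.30 | 0.55 | 6.38 | 70% |
| 0.25 | 0.46 | 4.43 | 55% |
| 0.20 | 0.37 | 2.83 | 38% |

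A simulation with 42 per group gave 91.1% at 0.40 and 38.1% at 0.20.

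**Step 4: sensitivity at 0.20 baseline SD.** Power is 30% at r = .80 and 53% at r = .90. With r = .85 it is 44% with no dropout, 42% with baseline adjustment and 52% with a one-sided 5% test (the last two by normal approximation). At r = .80, the retest level below which the article calls for double data entry, power for 0.40 baseline SD is 82%.

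**Step 5: expected precision.** The standard error of the difference in change is 0.548 × √(2 / 42.5) = 0.119 baseline SD. With t(83) = 1.989, the 95% half-width is 1.989 × 0.119 = 0.24 baseline SD.

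**The case against.** The best defence is that nothing was miscalculated. The inputs, software and test are disclosed, and the 90% reproduces. The word small is attached to an f whose value is printed beside it, f = 0.1 is itself conventionally called small, and the article makes no claim in units of SD. Nowhere does it define a small effect or name 0.20 SD as a target.

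Much of this stands. There is no arithmetic error, and the 38% matters only to a reader who takes 0.20 baseline SD as small. But the values 0.40 and 0.73 do not depend on that convention. They follow from the stated f and r and from the test, and they lie on the scales the article has chosen for reporting. The unconverted label hides them.

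A reader might also infer that the label is further off on the change scale than on the baseline scale. It is not: 0.20 baseline SD is 0.20 / 0.548 = 0.365 change SD, and 0.73 / 0.365 is again a factor of two.

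**Conclusion.** The description of the power claim is wrong as written, and the number is right. The trial has about 91% power for a difference in change of 0.40 baseline SD (0.73 change SD), and about 38% for 0.20 baseline SD. This rests on 84 or 85 completers, r = .85, equal SDs at both time points and a two-sided 5% test. None of the variations in Step 4 brings power at 0.20 baseline SD near 90%.

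Three stronger readings are tempting, and the documents do not support them.

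- *The trial is too small.* About 159 completers per group would be needed for 90% power at 0.20 baseline SD, but the article never sets 0.20 as its target.
- *The authors will take a null result as proof that there is no small benefit.* No passage says so. The article draws implications only from positive results and plans to report effect sizes.
- *A null result cannot exclude effects below about 0.39 baseline SD, the difference detectable with 90% power.* What a result excludes depends on its confidence interval. An estimate near 0 would have an upper limit of about 0.24. A just non-significant estimate of 0.23 would have one of about 0.47.

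Severity is moderate: the description needs correcting, while the sample size, test and analysis stand.

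**What to change.** In *Power analysis*, delete the word small and state the assumed effect on the article's two reporting scales: with 85 completers and r = .85, power is about 91% for a between-group difference in change of 0.40 baseline SD (0.73 change SD). Add the power at smaller differences, for example about 70% at 0.30, 55% at 0.25 and 38% at 0.20 baseline SD, and note that the last ranges from 30% to 53% for r from .80 to .90. State that a non-significant result will be interpreted from the confidence interval of the difference in change, with an expected 95% half-width of about 0.24 baseline SD. Do not add a fixed exclusion threshold.

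The cost is a few sentences and a less favourable power statement. No participants are added, and the primary test, alpha and conduct stay as they are.

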## Discussion

Our upcoming findings might have a clinical implication for adults over 50 years of age who have low puzzle experience in the past 5 years but are interested in solving jigsaw puzzles. As solving jigsaw puzzles depicts a low-cost, intrinsically motivating leisure activity, which can be executed alone or with others, and without the need to operate a digital device, positive results would indicate a highly feasible cognitive intervention to improve visuospatial cognition and everyday functioning, and psychological outcomes in this population. We will not investigate the effect of jigsaw puzzling on overall cognitive functioning including cognitive domains such as language or verbal working memory as generalization to non-trained cognitive domains cannot be expected from a theoretical and an empirical point of view [56, 57]. However, as visuospatial dysfunctions (e.g., deficits in visuoconstruction or visuospatial episodic memory and missed traffic signs or relocated objects) are common in neurocognitive diseases such as mild cognitive impairment and dementia - especially due to Alzheimer’s disease, dementia with Lewy bodies, and posterior cortical atrophy [23] - lifelong jigsaw puzzle experience might be one out of many cognitive activities that may contribute to a delayed clinical manifestation of neurocognitive disorders.

Limitations of the study design are the lack of a long-term follow-up and of the investigation of biological mediators, and the lack of participants’ blinding to group allocation, which could lead to differential expectation effects. In addition, the selected outcomes may have limitations in assessing the effects of jigsaw puzzling on cognitive abilities and daily functioning. Finally, the cognitive health counseling might have different behavioral effects in the counseling and the puzzle group that could mask the effects of jigsaw puzzling.

To address the lack of long-term follow-up, we will ask participants after study completion whether they will be interested in future long-term follow-up that we aim to conduct approximately 1.5 years after posttest assessment.

Blinding of participants is by nature not feasible in behavioral intervention studies as participants are always aware of what they are doing. Thus, expectation effects can never be fully excluded. Multiple approaches to minimize expectation effects will be used and participants’ expectations with regard to performance improvement will be measured in a telephone-based interview approximately 9 days prior to the posttest assessment. Thus, it will be possible to statistically account for potential expectation effects.

Even if not expected, the selected outcomes of the study may not cover the cognitive abilities that are actually engaged and improved through jigsaw puzzling (e.g., verbal working memory) or may include abilities that are not recruited and improved through the intervention (e.g., cognitive flexibility). To prevent this problem, the selection of the outcomes was based on a cognitive task analysis of jigsaw puzzling that indicated the expected cognitive demands [58, 59]. Furthermore, we will assess the association between the outcome measures and jigsaw puzzle skill at baseline, in order to validate the recruited cognitive abilities of jigsaw puzzling [60] and the transfer potential of gains in jigsaw puzzle performance on gains in the respective outcomes [61]. Finally, there is a not fully preventable risk that gains in outcomes may be a result of skill acquisition or newly learned strategies rather than the improvement of broad cognitive abilities [14]. However, in contrast to many previous cognitive training studies, we use a large set of transfer tasks and these task paradigms are substantially dissimilar from the training task. Thus, we avoid the risk that skill-induced or strategy-induced gains in single and structurally similar tasks with the training task will be misinterpreted as gains in broad cognitive abilities.

Finally, we cannot fully exclude that the cognitive health counseling intervention that is conducted in both groups may have a differential effect between the groups. However, we will assess this potential by evaluating group differences in behavioral changes in cognitive, physical, and social activities, and in Mediterranean diet. In additional analyses of the group effect on the study outcomes, we will statistically account for these behavioral changes (see “Statistical analysis”).

In the case of positive results, future research should investigate maintenance of effects, biological mechanisms of effects, potential effects in other populations such as people with impairments in visuospatial cognition, and effects of long-term experience in solving jigsaw puzzles on the prevention of neurocognitive disorders such as mild cognitive impairment and dementia.

## Abbreviations

AE: Adverse event
MMSE: Mini-Mental State Examination
MRT: Mental Rotations Test
PACE: Jigsaw Puzzles As Cognitive Enrichment
RSV: Ravensburger Spieleverlag GmbH
TIADL: Timed Instrumental Activities of Daily Living
TMT: Trail Making Test
